### **6.3.3 ART-free Follow-up Period**

#### **6.3.3.1 Visit 6**

This visit should be 112 ( $\pm 7$ ) days from Visit 2.

The following procedures will be performed:

- Recording date(s) of stopping ART
- Review of concomitant medications and AEs.
- Vital signs (blood pressure, heart rate).
- Clinical chemistry and hematology.
- Viral load, proviral DNA, CD4 and CD8 counts.
- T-cell response (ELISPOT, T-cell proliferative response assay and intracellular cytokine staining).

#### **6.3.3.2 Visit 7**

This visit should be 140 ( $\pm 7$ ) days from Visit 2.

The following procedures will be performed:

- Review of concomitant medications and AEs.
- Vital signs (blood pressure, heart rate).
- Clinical chemistry and hematology.

- Viral load, CD4 and CD8 counts.

#### **6.3.3.3 Visit 8**

This visit should be 168 ( $\pm 7$ ) days from Visit 2.

The following procedures will be performed:

- Review of concomitant medications and AEs.
- Vital signs (blood pressure, heart rate).
- Clinical chemistry and hematology.
- Viral load, CD4 and CD8 counts.

#### **6.3.3.4 Visit 9**

This visit should be 196 ( $\pm 7$ ) days from Visit 2.

At this visit it will be recommended that the subjects restart ART.

The following procedures will be performed:

- Review of concomitant medications and AEs.
- Physical examination including weight.
- Vital signs (blood pressure, heart rate).
- Clinical chemistry and hematology.
- Viral load, proviral DNA, CD4 and CD8 counts.
- T-cell response (ELISPOT, T-cell proliferative response assay and intracellular cytokine staining).

### **6.3.4 Follow-up Period to End of Study**

The follow-up period after restarting ART at Visit 9 consists of an 8-week period.

#### **6.3.4.1 Visit 10 (End of Study)**

This visit should be 252 ( $\pm 7$ ) days from Visit 2.

The following procedures will be performed:

- Review of concomitant medications and AEs.
- Physical examination including weight.
- Vital signs (blood pressure, heart rate).
- Clinical chemistry and hematology.
- Viral load, proviral DNA, CD4 and CD8 counts.

- T-cell response (ELISPOT, T-cell proliferative response assay and intracellular cytokine staining).

#### **6.4 Subject Discontinuation (Lost to Follow-up)**

In the event that a subject elects not to return to the clinic for the final study visit (End of Study), the Investigator must make every effort to contact the subject to review all AEs. In the event that a subject drops out of the study at any time, the reason for discontinuation must be fully documented in the source documents and the CRF. The site personnel will document the AEs and any other assessments in the source documents and will make every effort to complete all required End of Study assessments.

### **7 STUDY ASSESSMENTS AND MEASUREMENTS**

#### **7.1 Demographic and Screening Assessments**

The following information will be collected at the Screening Visit:

- Date of birth and the subject identification number from the Study CT-BI Vacc-4x 2007/1 (EudraCT Number 2007-006302-13). to verify the subject's participation in that study
- Medical history (from end of Study CT-BI Vacc-4x 2007/1) HIV-1 disease status as measured by viral load and CD4 and CD8 counts.
- ART medications and other concomitant medications.
- Clinical chemistry and hematology.

#### **7.2 Efficacy Assessments**

##### **7.2.1 Delayed-type Hypersensitivity – Test Administration**

DTH skin reactivity testing represents a simple *in vivo* method for monitoring cellular immune responses. The DTH test consists of Vacc-4x with a concentration of 4.0 mg/mL. At the pharmacy, a DTH dose is prepared to the final concentration of 4.0 mg/mL as described in the Pharmacy Manual. A volume of 0.1 mL should be drawn into a syringe ready for use. All handling of the product should be in compliance with handling of sterile product for injection. The reconstituted product should be used as soon as possible after preparation, and within a maximum of 8 hours when stored at 2 to 8°C.

DTH testing will be performed at the time of the first re-boost (Visit 2) and 2 weeks after last re-boost (Visit 4). An injection of 0.1 mL of a 4.0 mg/mL Vacc-4x should be administered intradermally at the front of arm; the DTH test does not require prior injection of adjuvant.

The DTH test results will be evaluated by study personnel or by the subject (as done in the previous study) 48 hours after the tests are performed. For each DTH test, evaluation of the injection site will include documentation of palpable skin induration and skin erythema. A positive DTH test is defined

as an area of induration or erythema  $\geq 10\text{mm}^2$  (length x height). Study personnel will record DTH results in the subject's source documents and transcribe them into the CRF.

### **7.2.2 CD4 and CD8 Counts**

A blood sample (approximately 4 mL) will be collected in tubes containing ethylenediamine tetraacetic acid (EDTA) at all visits in the study. CD4 and CD8 cells will be measured by flow cytometry. Tests will be performed at central laboratories in the US and in Europe. Handling of samples at the site will be detailed in laboratory manuals.

### **7.2.3 HIV Viral Load**

A blood sample (approximately 6 mL) will be collected in tubes containing EDTA at all visits in the study. Viral load will be quantified by HIV RNA copies/mL using polymerase chain reaction (PCR). Tests will be performed at central laboratories in the US and in Europe. Handling of samples at the site will be detailed in laboratory manuals.

### **7.2.4 Proviral HIV DNA**

To provide additional exploratory information on the HIV viral load, proviral HIV DNA will be analyzed at the central laboratory in Europe (Lausanne, Switzerland) on the same PBL samples mentioned in Section 7.2.5. Proviral DNA will be analyzed at Visit 2, 4, 6, 9 and 10 (End of Study). Handling of samples at the site will be described in detail in laboratory manuals.

### **7.2.5 T-cell Response**

Blood samples (approximately 60 mL) will be drawn and the peripheral blood lymphocytes (PBL) separated at each clinical trial site. The PBL will be frozen at  $< -70^\circ\text{C}$  and shipped frozen within 21 days of collection to the central laboratory in Europe (Lausanne, Switzerland) for evaluation. Handling of samples at the site will be detailed in laboratory manuals. The T-cell response to the p24 antigen (including Vacc-4x peptides) will be measured using an ELISPOT test, T-cell proliferation and intracellular cytokine staining at Visit 2, 4, 6, 9 and 10 (End of Study).

ELISPOT is a sensitive immunoassay that will enable detection of antigen-specific T-cells generated after Vacc-4x re-boosting compared with Visit 2 (before re-boosting).

Blood samples will also be analyzed by flow cytometry. Collected cells will be labeled with fluorescent dye (carboxyfluorescein succinimidyl ester [CFSE]), and upon antigen-challenge, activity (intracellular cytokines/ biomarkers, proliferation, T-cell receptor repertoire, surface activation markers) of antigen-specific cells will be visualized and quantified.

T-cell proliferative responses will be evaluated using the T-cell proliferation assay modeled after a previously reported assay ([Kvale, 2005](#)). T-cell proliferative responses will be compared with data reported in the initial study CT-BI Vacc-4x 2007/1 (EudraCT Number 2007-006302-13).

Results for intracellular cytokine testing will be presented in a single written report appended to the Clinical Study Report, to be prepared by the central laboratories. These outputs will be supplied directly to the Sponsor.

In addition, supernatant from the T-cell proliferation assay will be collected for further possible biomarker (e.g., cytokines) testing by Bionor Immuno AS in order to depict Vacc-4x induced T-cell responses. A single written report appended to the Clinical Study Report will be performed by Bionor Immuno AS.

### **7.3 Safety Assessments**

#### **7.3.1 Medical History**

The medical history from the time the subject finished the previous study (CT-BI Vacc-4x 2007/1; EudraCT Number 2007-006302-13) up to inclusion in this re-boosting study will be collected.

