### **4.2 Inclusion Criteria**

1. Completed immunization regimen with Vacc-4x active and stopped ART (at Week 28) in the CT-BI Vacc-4x 2007/1 study. (No re-start of ART is required).
2. Documented pre-study CD4 cell count  $\geq 400 \times 10^6/L$ .
3. Documented pre-study viral load  $< 300\,000$  copies/mL.
4. Signed informed consent.

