### **4.3 Exclusion Criteria**

A subject will not be eligible for this study if any of the following criteria apply:

1. Reported AIDS-defining illness within the previous year.
2. Malignant disease.
3. On chronic treatment with immune-suppressive therapy.
4. Unacceptable values of the hematologic and clinical chemistry parameters, as judged by the Investigator, including creatinine values  $> 1.5 \times$  upper limit of normal (ULN), and AST, ALT and alkaline phosphatase (ALP) values  $> 2.5 \times$  ULN.
5. Concurrent chronic active infection such as viral hepatitis B or C or tuberculosis.
6. Pregnant or breastfeeding women.
7. Women of childbearing potential not using reliable and adequate contraceptive methods (defined as: use of oral, implanted, injectable, mechanical or barrier products for the prevention of pregnancy; practicing abstinence; sterile) during the  $28 \pm 2$  days re-boosting period including the DTH and for 2 weeks after the DTH test, or sexually active male subjects with partners of child bearing potential unwilling to practice effective contraception during the  $28 \pm 2$  days re-boosting period including the DTH and for 12 weeks after the DTH-test.
8. Current participation in other clinical therapeutic studies.
9. Incapability of compliance to treatment protocol, in the opinion of the Investigator.

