### **6.3 Procedures by Study Phase**

#### **6.3.1 Screening**

##### **6.3.1.1 Screening Visit (Visit 1)**

Having given consent, subjects will undergo Screening assessments to determine whether they are eligible to participate in the study according to the criteria listed in Section 4.2 and Section 4.3. The following evaluations will be performed during Screening:

- Review of inclusion/exclusion criteria.
- ART status (on ART or not on ART), including drug name(s) and date(s) started.
- Medical history since end of study CT-BI Vacc-4x 2007/1 (EudraCT Number 2007-006302-13)
- Physical examination (including height).

- Vital signs (blood pressure, heart rate).
- Clinical chemistry and hematology (hemoglobin, C-reactive protein [CRP], white blood cells (WBCs), platelets, creatinine, AST (SGOT), ALT (SGPT), lactate dehydrogenase (LDH), ALP, gamma Glutamyl Transferase ( $\gamma$ -GT), albumin, total bilirubin,  $\beta$ 2-microglobulin).
- If restarted ART after Week 52 in CT-BI Vacc-4x 2007/1 study (EudraCT Number 2007-006302-13), last viral load before restart ART should be recorded.
- Viral load, CD4 and CD8 counts.
- Concomitant medications and AEs.

At the Investigator's discretion, laboratory tests may be ordered through a local laboratory to confirm a subject's current status regarding chronic active infections or AIDS-related illnesses in order to confirm eligibility in the trial if the status is not sufficiently documented in the subject's medical records.

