#### **6.3.2.1 Visit 2**

This visit will occur at least five days but not more than 28 days after the Screening Visit. The Visit 2 should occur after the results of the Screening evaluations are available to confirm eligibility.

The following procedures will be performed in the following order (it is important that all blood samples are taken before administration of study treatments):

- Review of concomitant medications and AEs.
- Physical examination including weight.
- Vital signs (blood pressure, heart rate).
- Urine pregnancy test (all females of child bearing potential).
- Clinical chemistry and hematology.
- Viral load, proviral DNA, CD4 and CD8 counts.
- T-cell response (ELISPOT, T-cell proliferative response assay and intracellular cytokine staining).
- Intradermal administration of Leukine®.
- Intradermal administration of Vacc-4x, 10 to 20 minutes after administration of Leukine®.
- Administration of DTH test (test to be evaluated 48 hours after administration).

The subject should remain in the clinic for 1 hour after the administration of study drug and the DTH test to be monitored for adverse reactions to the immunization.

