## **8 ADVERSE EVENT MANAGEMENT**

### **8.1 Non-serious and Serious Adverse Events**

The Investigator is responsible for the detection and documentation of events meeting the criteria and definition of an AE or SAE as provided in this protocol (see below). All AEs and SAEs that occur from the time written informed consent is obtained until completion of the study at Visit 10 must be documented. Information to be collected includes the description, date and time of onset and stop, intensity, duration, causality, seriousness relationship, outcome and action taken ([Section 8.1.4](#)). Even if the AE is assessed by the Investigator as not reasonably attributable to study drug, its occurrence must be recorded in the source documents and reported on the CRF.

During each study visit, after the subject has had an opportunity to spontaneously mention any problems, the Investigator should inquire about the occurrence of AEs. The following are examples of open-ended questions that may be used to obtain this information:

- “How are you feeling?”
- “Have you had any medical problems since your last visit/assessment?”
- “Have you taken any new medicines, other than those given to you in this study, since your last visit/assessment?”

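### No eligibility criterion or Visit 2 pre-dose rule considers reactions to Vacc-4x or GM-CSF in CT-BI Vacc-4x 2007/1, and the Screening history starts only after that study ended

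*Protocol*

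**What the plan says.** Entry requires earlier exposure. Inclusion criterion 1 in 4.2 reads "Completed immunization regimen with Vacc-4x active and stopped ART (at Week 28) in the CT-BI Vacc-4x 2007/1 study". Section 5.1.5 keeps the dose and immunization procedure of that study.

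Three places define the history to be collected, and all start it when 2007/1 ended: 6.3.1.1 ("Medical history since end of study CT-BI Vacc-4x 2007/1"), 7.1 ("Medical history (from end of Study CT-BI Vacc-4x 2007/1") and 7.3.1 ("The medical history from the time the subject finished the previous study"). Adverse event capture starts later still, under 8.1: "All AEs and SAEs that occur from the time written informed consent is obtained".

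Section 4.3 opens with "A subject will not be eligible for this study if any of the following criteria apply" and lists nine items. None names an earlier reaction, hypersensitivity or anaphylaxis to Vacc-4x or the adjuvant, and the ninth concerns compliance only. At Visit 2 (6.3.2.1) the one general safety review before the injections is "Review of concomitant medications and AEs". The other pre-dose steps are examination, vital signs, a pregnancy test and blood sampling.

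For reactions during the present study, 4.4.1.1 (severe or life-threatening local reactions) and 4.4.1.2 (related Grade 3 or 4 systemic reactions) hold further vaccine until the Medical Monitor and Sponsor have been consulted. Section 5.1.7 requires a permanent stop after anaphylaxis.

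**The concern.** The protocol sets its own thresholds for caution about giving this product again to someone who has reacted to it. In a re-boosting study, the earlier course is the main source of such information about each subject, and Visit 2 is the first re-exposure the protocol describes. Yet the thresholds are applied only from Visit 2 onward. A site could follow every written step and still re-dose a subject whose earlier reaction, had it occurred at Visit 2, would have held or cancelled the Visit 3 dose.

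What is at stake is the protection of individual subjects. No endpoint, analysis set or test is affected. For a severe local or related Grade 3-4 reaction, the missing step is a consultation, after which dosing may well go ahead. Only for anaphylaxis is the missing step a stop.

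**Working it through.** The protocol gives no figure to reproduce here, so the check sets its provisions side by side.

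**Step 1: does any required step bring out a 2007/1 reaction?**
- Screening history (6.3.1.1, 7.1, 7.3.1): no, it begins after 2007/1.
- Adverse event recording (8.1): no, it begins at consent.
- Inclusion criteria (4.2): only indirectly, through completion of the regimen.
- Exclusion criteria (4.3): no.
- Visit 2 pre-dose steps (6.3.2.1): no.
- Initial-study identifier: 7.1 collects "the subject identification number from the Study CT-BI Vacc-4x 2007/1", but its stated use there is to confirm that the subject took part.

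**Step 2: if a reaction came to light anyway, would a rule act on it?** No. The consultation rules in 4.4.1.1 and 4.4.1.2 and the stop in 5.1.7 are written for management during this study. Lengthening the history alone would therefore trigger nothing. The main cause is the missing eligibility or pre-dose rule, and the history window supports the gap.

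**Step 3: who passes inclusion criterion 1 despite a qualifying reaction?**
- *Mid-regimen reaction, dosing stopped:* the regimen was not completed, so the subject is filtered out.
- *Mid-regimen severe local or related Grade 3-4 systemic reaction, dosing continued:* the subject completed and is not filtered. Section 1.4 shows this can happen for local reactions. In Phase I one subject had severe ones, and no subject was withdrawn for a treatment-related event.
- *Any qualifying reaction at the last dose or a later DTH test:* not filtered. The last dose was at about Week 18. This is inferred from 1.3, where the rabbit schedule followed the clinical one up to that week. Section 2.2.1.2 also cites a Week 18 DTH response.

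**Step 4: exposure at Visit 2.** The re-boost is 0.1 mL × 12 mg/mL = 1.2 mg and the DTH test is 0.1 mL × 4.0 mg/mL = 0.4 mg, so 1.2 + 0.4 = 1.6 mg of Vacc-4x is given on one day. No threshold in the protocol makes 1.6 mg a concern. If the Week 18 dose and DTH test in 2007/1 fell on the same day, the combination is not new to these subjects either.

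**Step 5: how many subjects?** The protocol gives no 2007/1 reaction counts, grading scale or stopping rules. For 30 to 40 entrants (10.1) and an assumed share *p* with a qualifying reaction, the expected number is *np* and the chance of at least one is 1 − (1 − *p*)^*n*:
- *p* = 0%: 0 expected.
- *p* = 1%: 0.3 to 0.4 expected; 26% to 33% chance of at least one.
- *p* = 3%: 0.9 to 1.2 expected; 60% to 70% chance of at least one.

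These shares are assumptions that show scale only. The protocol supports none of them over the others.

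**The case against.** The case against is substantial. Completing the same regimen at the same dose selects for tolerance: anyone who reacted early was re-challenged and finished. Section 1.4 says 2007/1 raised no safety concern under a Data Safety Monitoring Board, and 1.1 describes the vaccine as safe and well tolerated. The 40-subject Phase II study, with 20 subjects at 1.2 mg, likewise reports no safety concern. The sponsor already holds the 2007/1 records, so not collecting that period again is reasonable. The investigator may withdraw a subject on safety grounds at any time, including before Visit 2 (4.4). Subjects know the treatment (1.6, 11.1), consent covers possible consequences (11.6.1), and one hour of observation follows each immunization (5.1.7).

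Most of this stands, and it is why the point is minor. It does not close the gap. The safety statements describe whole studies and give no counts, while the rules at issue act on individuals. Withdrawal is discretionary, awareness relies on recall, and observation comes after the injection. Nothing requires anyone to ask.

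A reader might go further in four ways that the protocol does not support:
- *That any subject who reacted in 2007/1 can be re-dosed.* Inclusion criterion 1 removes those whose regimen was stopped.
- *That the late-starting history is itself the cause.* Step 2 shows that extending it alone would change nothing.
- *That subjects with prior anaphylaxis are likely to enter.* No anaphylaxis to Vacc-4x is reported. Section 5.1.7 mentions only two transient vasovagal reactions in earlier human studies.
- *That the Phase I rate of severe local reactions (1 of 11, 9.1%, exact 95% interval 0.2% to 41.3%) predicts several affected entrants.* It came from 0.4 mg, 12 doses and molgramostim, against 1.2 mg and sargramostim here, and should not be projected onto this study.

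**Conclusion.** The point holds in limited form. As written, the protocol allows re-dosing of a subject who completed the 2007/1 regimen and had either a severe local or related Grade 3-4 systemic reaction after which dosing continued, or any qualifying reaction at the last dose or a later DTH test. The consultation or stop required for the same reaction in this study would not apply. This is a gap in the reach of the rules; no two sections contradict each other.

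The number affected is unknown and may be zero. The conclusion assumes that no document outside the protocol already requires a check of 2007/1 reactions. How many subjects fall in the gap depends on that study's stopping rules and reaction records, which are not available here. If 2007/1 also stopped dosing permanently after anaphylaxis, that part shrinks to reactions at the last dose or a later DTH test. Severity is minor: a precautionary safety improvement with no effect on the analysis.

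**What to change.** 1. In 6.3.2.1, add a pre-dose rule: for any reaction in 2007/1 that meets the 4.4.1.1 or 4.4.1.2 threshold, the Medical Monitor and Sponsor are consulted before the Visit 2 dose.
2. In 4.3, and in the matching synopsis list, add a precautionary exclusion for prior anaphylaxis to Vacc-4x or GM-CSF, in line with 5.1.7.
3. To support both, extend the history in 6.3.1.1, 7.1 and 7.3.1 to 2007/1 reactions to Vacc-4x, GM-CSF or the DTH test that meet these thresholds. Look them up with the initial-study identifier already collected. Expected DTH induration and erythema should not count. If 2007/1 used a different grading scale, its grades need mapping to the one used here.

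The cost is a few sentences and a look-up in 30 to 40 existing records, limited to events above the thresholds. The downside is that a subject may be delayed or not dosed in an already small study.

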#### **7.3.2 Physical Examination**

Physical examinations will be performed at Visit 1, 2, 5, 9 and 10 (End of Study). Physical examination will include height (only at Screening), weight and evaluation of the subject's medical condition. Any new or worsening of medical condition compared to the Visit 2 (first re-boosting dose) should be recorded as an AE on the CRF.

#### **7.3.3 Vital Signs**

At all visits in the study, vital signs (heart rate, systolic and diastolic blood pressure) will be measured prior to administration of study drug (if applicable) with the subject in the sitting position. Vital signs will be measured after the subject has been sitting at rest for 5 minutes.

#### **7.3.4 Clinical Laboratory Tests**

Blood samples will be collected (approximately 10 mL) at all visits in the study. It is important that blood samples are taken prior to administration of study treatments. For the European sites the blood samples will be sent to Covance laboratory in Geneva, Switzerland, for analysis. For the US sites the blood samples will be sent to Covance laboratory in Indianapolis, US, for analysis.

The following clinical chemistry and hematology parameters will be measured:

